After completion of the baseline questionnaires, participants will be randomized to one of the two study conditions (experimental or control group). Randomization will be carried out by an independent researcher in blocks of 10 participants within each ED unit (50% of patients from each block will be assigned to the experimental group and the other 50% to the control group), using a random allocation program. Allocation concealment will be also ensured.

After this, patients will be notified about the group they belong to during their next visit to the ED unit. At this time, patients from the experimental group will be given oral and written instructions about how to download and use the TCApp. ED specialists responsible for the online monitoring will be also taught the basic principles for using the application. In turn, patients from the TAU control group will be told that access to the TCApp will be offered to them after a waiting period of 6 months (T2 evaluation completed).

Then, each group of patients will receive the treatment that corresponds to them during a period of 12 weeks. At the end of the 12-week treatment, patients from the experimental group will stop using the TCApp and the evaluation post-treatment (T1, 12 weeks later) will be carried out, including: a) a brief clinical interview (patients), b) questionnaires (patients, informal caregivers, ED specialists); c) telephone interviews (technical staff, ED specialists) and d) focus groups with ED specialists of each institution who are interested in participating as well as with patients of the experimental group.

In the follow-up evaluation T2, 6 months after the beginning of treatment, patients, their informal caregivers and ED specialists responsible for the online monitoring will complete some questionnaires. In addition, telephone interviews will be conducted with ED specialists and a brief clinical interview will be carried out with patients. At the end of this phase, patients from the control group will be given access to the TCApp after being contacted by the ED specialist who will be responsible for their online monitoring.

Figure 1 presents the procedure and the timeline of the study and Table 1 provides a detailed description of the methodology with a definition of the study variables and their assessment tools.

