### Sample size calculation

The a priori sample size calculation was based on results from previous studies that implemented Internet-based programs in the treatment of EDs [58–60]. A small between-group effect size (Cohen’ s d = 0.40) is expected. The calculation was conducted by the software program G*POWER. The primary analysis will concern the hypothesis that the average level of eating pathology at post-intervention in the control group, based on the EDE-Q scores, will be higher than the average levels of eating pathology in the experimental group. Assuming an alpha of 0.05 and a power of 0.80 (β − 1) in an independent samples one-way t-test study, a minimum of 100 participants would be required per study arm. Allowing for a dropout rate of 25% of study participants from baseline, a total of 250 participants need to be recruited.

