### Statistical analysis

Both intent-to-treat and completers analyses will be carried out. Intent-to-treat analysis will include every participant who will be randomly allocated to one of the study conditions, that is to say, 250 patients. Whenever possible, we will try to collect follow-up data from participants who have dropped out, in order to keep our dataset as complete as possible. Baseline differences between completers and dropouts will be analysed (Pearson’s chi-square test Student’s t test) using data from the clinical interviews and the baseline questionnaires and possible reasons for dropout will be examined through interviews with the ED specialists (T1, T2).

A participant will be considered a completer if he/she has completed the initial clinical interview as well as T0 and T1 evaluations. For participants from experimental group, to be considered completers they will have to have used the TCApp at least 70% of the time that was initially agreed upon before the start of the experiment (at least once a day during a period of 12 weeks). Only data from completers will be used to determine the treatment effect on the main outcome variable.

All analyses will be carried out using SPSS (Statistical Package for the Social Sciences). First, we will examine the data using descriptive statistics. Between-group analysis will be conducted using Pearson’s chi-square test or Fisher’s exact test for categorical data and Student’s t test or the Mann-Whitney U test for continuous variables, depending on the normality of the distribution. The normality of the distribution of the variable will be assessed using the Kolmogorov-Smirnov test. The effect of the intervention in terms of reduction in the primary and secondary outcome measures over time will be computed by using a mixed model linear regression analysis with time, experimental condition and their interaction as independent variables. Since there may be some heterogeneity in the implementation of the intensive online intervention across the different participating institutions, between-centre heterogeneity will be explored in subgroup analyses.

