## Discussion

In this article  we present the protocol of a study aimed to assess the clinical efficacy of an intensive intervention program using the TCApp. In addition to the assessment of changes in ED pathology and other secondary outcomes, such as anxiety, depression and quality of life of both patients and their caregivers, we will assess the differential cost-effectiveness of an intensive treatment (TCApp + TAU) compared to that of TAU. This is an important strength of this study because to our knowledge, there are only a few apps for mental disorders with supporting evidence from RCTs and none of them was specifically designed for people with EDs or ED professionals [11, 61]. Once the TCApp has proven to be an efficient and cost-effective tool for use in ED units in Spain, the long-term contributions of the current study are as follows: 1) to promote the clinical use of the TCApp in ED units not only in Spain but also on an international level, 2) to improve the quality of patient care using the TCApp as complementary tool alongside face-to-face psychological treatment, while reducing direct and indirect costs associated with the treatment of the illness and 3) to explore the future use of the application in other mental disorders whose treatment is based on CBT, such as depression, addictions and anxiety.

Among the strengths of the study is its large sample size, which is clinically relevant, as it will be recruited from different public and private ED units in Spain. Another strength is the use of face-to-face assessment and a diagnostic interview to establish patient’s clinical diagnosis and confirm his/her final inclusion in the study, according to the inclusion and exclusion criteria. Furthermore, the assessment of the experience of caregivers is another strength worth mentioning.

Regarding the limitations of the study, the short follow-up time as well as the delayed access to the TCApp by the control group, which may influence our results, should be mentioned. Finally, a limitation related to the nature of the study is the fact that it is a multi-centre study that includes several private and public ED units in Spain. To overcome this limitation, when performing the statistical analyses, between-centre heterogeneity will be explored in subgroup analyses.

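### Allocation is blocked within each ED unit, but the stated outcome analyses leave unit out, and the Discussion wrongly treats exploratory centre subgroups as the remedy

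*Protocol article*

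**What the plan says.** Three places in the protocol article bear on this.

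- **Procedure and randomization.** Allocation is done "in blocks of 10 participants within each ED unit", half of each block to each arm. Unit is therefore a stratification factor by design.
- **Sample size calculation.** The primary hypothesis compares mean EDE-Q between arms at post-intervention. It is sized "in an independent samples one-way t-test study", with no allowance for unit.
- **Statistical analysis.** The mixed model has three independent variables: time, arm and the product of the two. Unit is not among them, nor is it in the simple between-group tests listed just before. It enters only in the next sentence, on heterogeneity of implementation: "participating institutions, between-centre heterogeneity will be explored in subgroup analyses".

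The Discussion then names the multi-centre structure as a limitation and gives the remedy: "To overcome this limitation, when performing the statistical analyses, between-centre heterogeneity will be explored in subgroup analyses".

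**The concern.** Balancing the arms within each unit removes differences between units from the treatment comparison. An analysis that ignores unit puts that variance back into the error term, so the reported precision is not the precision of the design.

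The protocol gives reasons to expect units to differ. The Sample section lists public and private services, among them a children's hospital, general hospitals, a regional health service and a specialised ED institute. Patients may be minors or adults, in day-hospital or outpatient care, of any severity.

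The Discussion's remedy addresses a different question. Looking at each centre separately asks whether the effect varies. It does nothing to the pooled estimate, its standard error or its p-value. At stake are some precision in a trial sized with little to spare, and a claim that a limitation has been dealt with when it has not.

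**Working it through.** **1. The plan's own figure.** Inputs from the Sample size calculation: "d = 0.40) is expected"; "Assuming an alpha of 0.05 and a power of 0.80"; result "a minimum of 100 participants would be required per study arm". The two-sided t-test solution is 99.08 per arm, rounded up to 100, so the figure reproduces. One-sided would need 78, so the test must be two-sided. The total of 250 equals 200 × 1.25. Unit plays no part.

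**2. Comparison at T1.** Take total SD = 1 and let ICC be the share of T1 variance lying between units. The document gives no ICC, so the values below are assumptions. With arms balanced within unit:

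- true SE = √(2(1 − ICC)/n)
- SE reported without unit ≈ √(2/n)
- ratio = 1/√(1 − ICC)
- actual two-sided alpha = 2[1 − Φ(1.96/√(1 − ICC))]

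With n = 100 per arm and d = 0.40:

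| ICC (assumed) | SE ratio | Actual alpha | Power, unit omitted | Power, unit included |
|---|---|---|---|---|
| 0.02 | 1.010 | 0.048 | 0.810 | 0.815 |
| 0.05 | 1.026 | 0.044 | 0.814 | 0.827 |
| 0.10 | 1.054 | 0.039 | 0.820 | 0.846 |
| 0.15 | 1.085 | 0.034 | 0.827 | 0.866 |

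The loss runs from 0.5 to 3.9 points. If 25% of 250 are lost, 250 × 0.75 / 2 ≈ 94 per arm remain, and the gains from including unit are about 1.4, 2.9 and 4.3 points at ICC 0.05, 0.10 and 0.15.

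A simulation with eight unequal centres, blocks of 10 and 20% random loss agrees at ICC 0.10: type I error 0.035 without unit and 0.045 with it; power 0.819 and 0.844. The formula is an upper guide. A simulation at ICC 0.15 with 25% loss gave SEs of 0.1416 and 0.1340, a ratio of 1.057 rather than 1.085.

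**3. Time-by-condition interaction.** Write the outcome of patient i in unit j at visit t as unit effect c_j + patient effect p_i + time and treatment terms + error. In T1 minus T0, both c_j and p_i cancel. A unit effect constant over time therefore never enters the interaction's standard error, and a unit main effect has nothing to remove. Simulations at ICC 0.15 with a patient random intercept show this:

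- complete data: SE 0.1129 without unit, 0.1129 with it;
- 25% loss at T1: 0.1189 and 0.1186 (ratio 1.003).

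Only if units differ in change over time does something remain, and then it takes a unit-by-time term to remove it: 0.1322 and 0.1292 (ratio 1.023).

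**4. Centre subgroups.** The Sample section names eight services; one is regional and could hold more than one unit. Assuming equal size:

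- 250/8 = 31.25 patients, 15.6 per arm: power 0.19 for d = 0.40; detectable d at 80% power 1.04; 95% CI half-width 0.73 SD.
- 200/8 = 25 patients, 12.5 per arm: power 0.16; detectable d 1.17; half-width 0.83 SD.

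Unequal recruitment makes the smallest centres worse.

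**The case against.** The strongest reply is that the stated model tests change over time, and the hypotheses in the Background are worded as change scores. For that contrast the effect of a constant centre difference is about nil, and adding only a unit main effect gains nothing. This stands. A reader might infer that the mixed model's interaction has a standard error up to 8.5% too large; step 3 shows it does not. The T1 figures apply because the Sample size calculation defines the primary analysis as a between-group comparison at post-intervention.

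Second, the error is conservative and its size is assumed. This stands too. A reader might infer inflated false positives or a biased effect; neither follows from leaving out a balanced stratification factor. At ICC 0.02 the loss is trivial.

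Third, the subgroups are described as exploratory, and the article specifies no per-centre significance test. One could compute 1 − 0.95^8 = 0.34 as the chance of at least one false-positive centre, but that assumes eight separate tests at 0.05, which the article does not state. The figure should not be held against the plan. The low power per centre needs no such assumption.

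Fourth, an article condenses, and a random centre effect would not necessarily be listed as an independent variable. This has some force for the model sentence. It does not rescue the Discussion, which states how centre is to be handled and claims that this suffices.

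Finally, a unit term does not cover variation in the treatment effect itself. With a between-centre SD of 0.2 in the effect, simulated type I error for a zero average effect was about 0.08 to 0.09 with or without a unit main effect. The fix below should not be presented as curing that.

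**Conclusion.** The point holds in a limited form. The design stratifies by unit, the stated analyses do not reflect it, and the Discussion is wrong that exploratory centre subgroups overcome the multi-centre limitation.

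For the T1 comparison the cost is a standard error about 1-8% too large and roughly 0.5-4 points of power. This rests on an assumed ICC of 0.02-0.15 and on arms staying nearly balanced within units. For the time-by-condition interaction the cost is about nil unless centres differ in change over time. The subgroups, at about 16-19% power each if eight centres recruit equally, can neither establish nor exclude heterogeneity.

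The validity of the main test is not threatened by this omission. The change is worth making because it is nearly free and because the Discussion claim is incorrect as written.

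**What to change.** - **Main analysis.** Either analyse T1 EDE-Q with ED unit and baseline EDE-Q as covariates, or include ED unit and ED unit-by-time in the mixed model. A unit main effect alone in the mixed model is not enough to change the interaction. Use the same structure for the secondary patient outcomes.
- **Small units.** State a rule for pooling very small units, set before outcomes are seen by arm.
- **Heterogeneity.** Replace the separate centre subgroups with one exploratory centre-by-condition term, or with shrunken centre estimates shown together.
- **Discussion.** Remove the claim that the subgroup analyses overcome the multi-centre limitation. Say that unit is accounted for in the main analysis and that variation in effect across units is explored with low power.

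Unit is already recorded for the randomisation and EDE-Q is already collected at T0, so no new data are needed. The cost is a few extra model terms, a few degrees of freedom and some redrafting. The sample size need not change on this account.

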### Economic evaluation

A cost-effectiveness analysis of the TCapp will be performed, which will compare the effects and costs of the intensive online intervention (TAU + TCapp) with the ones for TAU. The effects will be measured with quality-adjusted life years (QALYs) obtained from the EQ-5D-5 L and EQ-5D-Y questionnaires. Furthermore, the effects regarding the primary outcome variables (EDE-Q, SEED) will also be taken into account. On the other hand, costs will cover the development of the App, the costs of using the product, and the medical costs (visits and medication) for both groups. Moreover, societal costs such as productivity losses and the caregiving burden will also be assessed. Information on costs will be obtained from the iMTA questionnaire and from interviews with the clinicians and technicians. This evaluation will determine the incremental costs and effects of the intensive intervention compared to the control condition , and will produce an incremental cost-effectiveness ratio (ICER). 

## Discussion

In this article  we present the protocol of a study aimed to assess the clinical efficacy of an intensive intervention program using the TCApp. In addition to the assessment of changes in ED pathology and other secondary outcomes, such as anxiety, depression and quality of life of both patients and their caregivers, we will assess the differential cost-effectiveness of an intensive treatment (TCApp + TAU) compared to that of TAU. This is an important strength of this study because to our knowledge, there are only a few apps for mental disorders with supporting evidence from RCTs and none of them was specifically designed for people with EDs or ED professionals [11, 61]. Once the TCApp has proven to be an efficient and cost-effective tool for use in ED units in Spain, the long-term contributions of the current study are as follows: 1) to promote the clinical use of the TCApp in ED units not only in Spain but also on an international level, 2) to improve the quality of patient care using the TCApp as complementary tool alongside face-to-face psychological treatment, while reducing direct and indirect costs associated with the treatment of the illness and 3) to explore the future use of the application in other mental disorders whose treatment is based on CBT, such as depression, addictions and anxiety.

Among the strengths of the study is its large sample size, which is clinically relevant, as it will be recruited from different public and private ED units in Spain. Another strength is the use of face-to-face assessment and a diagnostic interview to establish patient’s clinical diagnosis and confirm his/her final inclusion in the study, according to the inclusion and exclusion criteria. Furthermore, the assessment of the experience of caregivers is another strength worth mentioning.

Regarding the limitations of the study, the short follow-up time as well as the delayed access to the TCApp by the control group, which may influence our results, should be mentioned. Finally, a limitation related to the nature of the study is the fact that it is a multi-centre study that includes several private and public ED units in Spain. To overcome this limitation, when performing the statistical analyses, between-centre heterogeneity will be explored in subgroup analyses.

## Abbreviations

AN: Anorexia Nervosa
ANSOCQ: Anorexia Nervosa Stages of Change Questionnaire
BDI: Beck Depression Inventory
BED: Binge Eating Disorder
BHS: Beck Hopelessness Scale
BN: Bulimia Nervosa
BNSOCQ: Bulimia Nervosa Stages of Change Questionnaire
CBT: Cognitive Behavioural Treatment
COI: Cost Of Illness
CSQ-8: Client Satisfaction Scale
DSM: Diagnostic and Statistical Manual of Mental Disorders
ECI: Experience of Caregiving Inventory
EDE: Eating Disorder Examination Interview
EDE-Q: Eating Disorder Examination Questionnaire
EDs: Eating Disorders
ICER: Incremental Cost-Effectiveness Ratio
K-SADS-S-PL: Schedule for Affective Disorders and Schizophrenia-Present and Lifetime version
QALYS: Quality-Adjusted Life Years
RCT: Randomised Controlled Trial
SCID-1: Structural Clinical Interview for Axis 1
SEED: Short Evaluation of Eating Disorders
SIS: Suicide Intent Scale
SPSS: Statistical Package for the Social Sciences
STAI: State-Trait Anxiety Inventory
SUS: System Usability Scale
TAU: Treatment As Usual
UOC: Open University of Catalonia
VAS: Virtual Analogue Scale
